**Table 4 Tab4:**
[figure not shown]
The telephone follow-up list

**Table 5 Tab5:**
[figure not shown]
The outpatient follow-up list

Legend; *CT* computed tomography, *MRI* magnetic resonance imaging

### Safety monitoring

The independent Data and Safety Monitoring Board (DSMB) will supervise safety during the trial. The members of DSMB are independent of the sponsor and trial investigators and have no competing interests. The DSMB will review and evaluate clinical safety and efficacy data collected according to the specified time intervals in the protocol. If the threshold of the safety data exceeds a predefined threshold, the DSMB will be notified. Furthermore, the DSMB will conduct the interim analysis of all AE occurrences every 6 months during the study. Only the data managers and study designers have access to the data in the trial. The data will be locked by the Data Management Team when the trial is completed. All of the data will be provided to the DSMB. If the trial is terminated earlier than the expected end date, the DSMB will contribute to that decision.

### Data collection

The data generated during the trial will be recorded in the original medical record and the CRF. The quality control personnel will check the consistency of the CRF data with the original record to ensure that the data are accurately entered into the CRF. There are nine data collection points: baseline, 1 day, 3 days, 7 days, 1 month, 3 months, 6 months, 12 months, and 24 months (Table 2). Within 3 days after completion of the data collection, the research records will be submitted to the research leader for review and all data will be submitted to the project leader within 10 days. Next, the auditor will review each original research record to confirm that the clinical trial data records are timely, precise, and standardized. Data checks and entries will then be disposed by the statistical data manager and analyzed by the statisticians.

The data of this trial will be disseminated through national and international conferences and peer-reviewed publications. Our data set will be available after the trial’s completion.

### Statistical analysis

SPSS version 17 (SPSS Inc., Chicago, IL, USA) statistical analysis software will be used to analyze the data in the study. Significant differences will be considered at an α level of 0.05.

The data will be examined at group assignment to the intervention and control groups using the *χ*^2^ test, *t* test or analysis of variance (ANOVA). For the intervention and control groups, the indicators at baseline and at 1 day, 3 days, 7 days, 1 month, 3 months, 6 months, 12 months, and 24 months will be compared with repeated measures ANOVA. Comparison of these outcome indicators including duration of oxygen therapy, duration of mechanical ventilation, pulmonary function tests, and quantitative scores of chest radiography changes between the intervention and control groups will be conducted using the *t* test. Mortality and hospital readmission rates will be tested by the *χ*^2^ test, while 24-month mortality will be analyzed by Kaplan-Meier curves.

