### Outcome evaluation

The outcome measures and their time frames of this trial are listed in Table 3. The primary endpoint is the cumulative duration of oxygen therapy, i.e., the duration from starting to stopping oxygen treatment.

**Table 3 Tab3:** Outcome measures

Measures			Time frames
Primary outcomes	Cumulative duration of oxygen therapy		Until the time of stopping oxygen therapy
Secondary outcomes	Adverse events	Number of serious adverse events	Within 24 h post hUC-MSCs infusion
		Acute infusion associated adverse events	From the start of the trials to 1 month post hUC-MSCs infusion
		Late infusion associated adverse events	Within 2 years post hUC-MSCs infusion
	The rate of supplemental oxygen therapy		At 1 month post hUC-MSCs infusion
	Duration of invasive mechanical ventilation		
	Duration of noninvasive mechanical ventilation		
	The first time of stopping oxygen supplement		
	The rate of re-oxygen supplement		
	Pulmonary function changes		At 6, 12, and 24 months post hUC-MSCs infusion
	Chest radiography changes		
	Blood oxygen saturation		At 1, 3, 6, 12, and 24 months post hUC-MSCs infusion
	Mortality		
	Times of hospital readmissions		
	Complications of preterm birth		

The secondary endpoints include the safety and efficacy outcomes. The safety of the study will be assessed by the number of AEs including SAEs, acute infusion-associated AEs (AIA-AEs) and late infusion-associated AEs (LIA-AEs). SAEs include death, any malignant cardiac event (new ventricular tachycardia, ventricular fibrillation, or asystole, cardiac arrest), acute pulmonary embolism, stroke, anaphylactic shock, acute transplant rejection, and any other diseases extending the hospital stay. AIA-AEs include fever, general allergic reaction (rash, edema, erythema, pallor), infection at the injection site, vital sign changes, laboratory test changes (indicators of liver and kidney function, cardiac markers, indicators of hematology and immunity, markers of hepatitis/syphilis/HIV/tuberculosis, and urinalysis). LIA-AEs include tumorigenic events (tumor formation) and teratogenic events.

The efficacy endpoints are as follows: duration of oxygen therapy, duration of invasive mechanical ventilation, duration of noninvasive mechanical ventilation, the first time stopping the supplemental oxygen, rate of re-oxygen supplement, blood oxygen saturation, chest radiography changes, pulmonary function changes, mortality, number of hospital readmissions, and preterm birth complications.

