### Follow-up procedures

Follow-up assessments will be performed at 1, 3, 6, 12, and 24 months after the hUC-MSC injection (Table 2). The five follow-up points will be conducted by telephone and outpatient contact. The first two follow-ups will be performed at 1 and 3 months after the hUC-MSC treatment by telephone to ask the parents of the condition of their child(ren). The details of the telephone interview are shown in Table 4. The next three follow-ups will be performed at 6, 12, and 24 months at outpatient visits as shown in Table 5. The key outcome during follow-up will be changes on chest radiographs.

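### Lung function and chest imaging scores are compared by t test with no baseline adjustment, the nine-point repeated measures ANOVA fits the visit schedule poorly, and Table 3 lists saturation at two visits where Table 2 schedules none

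*Protocol article*

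**What the plan says.** The Data collection section sets the time grid: "There are nine data collection points: baseline, 1 day, 3 days, 7 days, 1 month, 3 months, 6 months, 12 months, and 24 months". The Statistical analysis section repeats that grid for a set of indicators it does not name and ends the sentence with "12 months, and 24 months will be compared with repeated measures ANOVA".

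The next sentence of that section gives the between-group comparison for several outcomes, including "pulmonary function tests, and quantitative scores of chest radiography changes between the intervention and control groups will be conducted using the" t test. No covariate is named. The significance level is given as "Significant differences will be considered at an α level of 0.05".

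Table 2 (Recruitment section) shows what is measured when. Chest CT and lung function are ticked at baseline, 6, 12 and 24 months. Blood oxygen saturation is ticked at baseline, 24 hours, 3 days, 7 days, 6, 12 and 24 months.

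Table 3 (Outcome evaluation section) gives the saturation outcome the time frame "At 1, 3, 6, 12, and 24 months post hUC-MSCs infusion". The Follow-up procedures section states: "The first two follow-ups will be performed at 1 and 3 months after the hUC-MSC treatment by telephone".

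**The concern.** There are three separate issues.

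- **Baseline.** Lung function and imaging are measured before treatment, and imaging change is named as the key outcome of follow-up. A plain t test either leaves the baseline value out or subtracts it in full. Regression on the baseline value is at least as precise as both. With 24 children per arm, that precision is worth having.
- **Complete cases.** In its standard form, repeated measures ANOVA drops a child who lacks any time point in the analysis. This is a property of the method, not something the document says. The plan itself allows for 10% loss to follow-up and describes a disease with substantial mortality, so incomplete records are foreseeable. The nine-point grid also does not match what Table 2 schedules for most indicators.
- **Saturation.** Two of the five time points listed for a secondary outcome have no scheduled measurement behind them. An analysis plan cannot repair that.

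**Working it through.** **The plan's own figure.** The Sample size section uses an SD of 15 days, a difference of 13 days (90 to 77), two-sided α of 0.05 and power of 0.80:

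2 × (1.96 + 0.84)² × 15² / 13² = 20.9, so 21 per arm; 21 / 0.90 = 23.3, so 24.

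Both stated figures reproduce and are not in dispute. They concern the primary outcome. The 24 per arm is used below only as the starting count.

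**Schedule against the nine-point grid (Table 2).**

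| Indicator | Points scheduled, of nine |
|---|---|
| Ventilator parameters/oxygen therapy; adverse events | 9 |
| Blood oxygen saturation | 7 (not 1 or 3 months) |
| Vital signs, which include transcutaneous saturation | 7 (not 1 or 3 months) |
| Chest CT | 4 |
| Lung function | 4 |

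Chest CT is taken as the source of the imaging score, because Table 2 schedules no other chest imaging.

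**Value of baseline adjustment.** Let r be the correlation between baseline and follow-up. The documents give no value, so a range is shown. With equal SDs at both times, and ignoring the one degree of freedom spent, the variances relative to a follow-up value are:

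- follow-up only: 1
- change score: 2(1 − r)
- baseline-adjusted: 1 − r²

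The ratio of adjusted to follow-up-only variance is 1 − r². The ratio of adjusted to change-score variance is (1 − r²) / (2(1 − r)) = (1 + r)/2.

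| r | Ratio to follow-up only | Reduction | Ratio to change score | Reduction |
|---|---|---|---|---|
| 0.3 | 0.91 | 9% | 0.65 | 35% |
| 0.5 | 0.75 | 25% | 0.75 | 25% |
| 0.7 | 0.51 | 49% | 0.85 | 15% |

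At r = 0.5, 24 children per arm carry the information of 24 / 0.75 = 32 under either reading of the t test.

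**Complete cases under the ANOVA.** Assume an independent miss rate m per post-baseline visit of 3% or 5%, before deaths. The documents give no such rate. The share complete is (1 − m)^k for k post-baseline visits.

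- Nine-point indicator, k = 8: 0.97⁸ = 0.784 and 0.95⁸ = 0.663. Times 24, this is 18.8 and 15.9.
- Indicator with three post-baseline visits, k = 3: 0.97³ = 0.913 and 0.95³ = 0.857. Times 24, this is 21.9 and 20.6.

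The difference detectable with 80% power in a two-arm contrast is 2.80 × √(2/n) SD. It is 0.81 SD at n = 24 and 0.99 SD at n = 16.

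**Saturation.** Table 3 lists 1, 3, 6, 12 and 24 months. In Table 2, both rows that could hold a saturation value are blank at 1 and 3 months. Follow-up procedures makes those two contacts telephone interviews with the parents. If the nine-point ANOVA were applied literally to saturation, no child could have a complete record.

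**The case against.** The case on the other side is substantial, and several parts of it stand.

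- A reader might infer that every analysis discards a child with one missed visit. It does not. Imaging and lung function are assigned to the t test, which loses a child only at the time compared. The 19-16 of 24 figure therefore applies to no imaging or lung-function analysis.
- A reader might infer that baseline is ignored. The ANOVA includes it as a level of time. The imaging score is described in terms of change, and Table 3 speaks of changes in lung function, so the t test may already subtract baseline. What remains is that no adjustment for baseline is specified, and adjustment gains precision under either reading.
- The nine-point list may mean each indicator at its own scheduled points. In a condensed article that is a natural reading. It reduces the mismatch with Table 2 but does not change how standard repeated measures ANOVA treats incomplete records.
- A 3-5% miss rate at every visit is an assumption. At eight visits it implies 22-34% incomplete, against the 10% loss the plan allows for. Three of those visits fall in the first week, where misses may be rarer.
- Covariates and missing-data rules are often left to an analysis plan, and their absence is no finding. The point rests on the methods that the article does name.

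**Conclusion.** The concern holds in limited form, for secondary outcomes. The primary outcome and the sample size are untouched.

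The firmest analytic point is baseline adjustment. The direction of the gain does not depend on how the t test is read, but its size depends on r: from 9% to 49% of variance against follow-up values, and from 35% down to 15% against change scores. The complete-case loss is real for whatever is analysed by the ANOVA. It is modest with three post-baseline visits (about 22-21 of 24 remain) and larger with eight (about 19-16), under the assumed miss rates and before deaths. Deaths are left out of these counts because the document does not say how much of the mortality it cites would fall between enrolment and month 24.

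The saturation conflict needs no assumption: Table 3 disagrees with Table 2 and with Follow-up procedures. It is tempting to say that the 1- and 3-month values cannot be obtained. The documents do not support that, because the telephone list (Table 4) is not shown. What is certain is that Table 2 schedules none. Nor does the Statistical analysis section name saturation, so this is an inconsistency in the schedule rather than an error in the analysis method.

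**What to change.** **Analysis.** Replace the repeated measures ANOVA, and the t tests for lung function and imaging score, with a likelihood-based linear mixed model. It should have terms for arm, visit, arm-by-visit and the baseline value, and use each indicator only at the visits Table 2 schedules. Report arm differences at 6, 12 and 24 months for lung function and imaging. Report deaths by arm beside these results, because the model treats values after death as if they were merely missing and so does not resolve truncation by death.

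**Schedule.** Reconcile Table 2, Table 3 and Follow-up procedures on saturation at 1 and 3 months. Give saturation its own time-frame row in Table 3. In the table as extracted, its time frame appears to be shared with mortality, readmissions and complications of preterm birth. Deleting 1 and 3 months from a shared cell would remove those time points from the other three outcomes, and Table 2 does tick mortality and complications at both visits.

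**Cost.** Rewording of the analysis section, a split table row and some extra analysis work. The model relies on a missing-at-random assumption, which should be stated. The analysis change needs no new data and no change to the design.

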### Sample size and calculation

The sample size of this phase-II randomized controlled trial was calculated by power analysis using the Power and Sample Size online calculator (http://powerandsamplesize.com/). The trial is designed to investigate the hypotheses of two interventions compared to control, but it is not powered to test differences between the two intervention groups. The larger of the two numbers is the sample size of this trial. The primary outcome measure is the change in the cumulative duration of oxygen therapy. The cumulative mean duration of severe BPD is reportedly 90 ± 15 days [4, 31]. This trial is powered to identify differences of 15% (from 90 days in the control group to 77 days in the low-dose groups) and 20% (from 90 days in the control group to 72 days in the high-dose groups) in participants who accept the hUC-MSC intervention. Meanwhile, the power is set at 0.8, type I error *ɑ* is 0.05, and type-II error *β* is 0.20. The calculated sample size is 21 for each group. To account for the possibility of 10% of patients being lost to follow-up, the final sample size will be 24 and the total size will be 72.

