		− 2 weeks	Baseline	24 hours	3 days	7 days	1 month	3 months	6 months	12 months	24 months
Therapy	hUC-MSCs	√	√								
	Traditional treatment	√	√	√	√	√					
Informed consent		√									
Inclusion and exclusion criteria		√	√								
Demographic information		√									
Personal history/past history/family history		√					√	√	√	√	√
Height/weight/head circumference		√	√			√	√	√	√	√	√
Vital signs^a^/physical examination		√	√	√	√	√			√	√	√
Hematology^b^/blood biochemistry^c^/urinalysis^e^		√	√	√							
Infectious disease-related examination^d^		√	√	√							
Blood oxygen saturation/blood gas analysis			√	√	√	√			√	√	√
Chromosome examination		√									
Brain MRI examination		√							√	√	√
EKG		√	√	√							
Echocardiogram		√									
Ventilator parameters/oxygen therapy			√	√	√	√	√	√	√	√	√
Adverse events evaluation			√	√	√	√	√	√	√	√	√
Chest high resolution CT			√						√	√	√
Pulmonary function test			√						√	√	√
Mortality/complications of prematurity^f^							√	√	√	√	√

Legend: *CK-MB* creatine kinase-MB*, CT*, computed tomography *EKG* electrocardiogram, *hUS-MSCs* human umbilical-cord mesenchymal stem cells

^a^The indicators of vital signs include temperature, blood pressure, heart rate, respiratory rate, transcutaneous oxygen saturation

^b^The condition of hematology of participants will be estimated by hematological tests which contains white blood cell count, platelet count, red blood cell count, hemoglobin, the percentage of lymphocytes, the percentage of neutrophil and C-reactive protein (CRP)

^c^The items of blood biochemistry include liver function, renal function, cardiac markers, the indicators of immunity, and the detailed items of each test are listed as follow. Liver function tests: albumin, bilirubin, alkaline phosphatase, alanine aminotransferase, aspartate aminotransferase, prothrombin time, activated partial thromboplastin time. Renal function tests: creatinine, blood urea nitrogen, creatinine clearance, glomerular filtration rate. Cardiac markers: hypersensitive troponin I, CK-MB mass, myoglobin

^d^Infectious disease-related examination include markers of hepatitis/syphilis/HIV/tuberculosis

^e^The content of urinalysis includes pH, protein, specific gravity, glucose and ketone bodies, white blood cells, occult blood or red blood cells, nitrite, color, and turbidity

^f^Complications of prematurity include growth retardation or retardation, hearing abnormalities, retinopathy, pulmonary hypertension, left ventricular hypertrophy

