### Randomization and blinding

Participants will be randomized into three groups in a 1:1:1 ratio after collection of the baseline data. The allocation sequence will be generated and sent to the investigators by a statistician. Participants will not be blinded during the phase-II trial and the patients in the control group will not be given hUC-MSC treatment.

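### The primary t test on oxygen duration is valid but ignores respiratory support recorded before randomisation; adjusting for it would add about 3 to 15 points of low-dose power, depending on an unstated correlation

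*Protocol article*

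**What the plan says.** Outcome evaluation defines the endpoint: "The primary endpoint is the cumulative duration of oxygen therapy, i.e., the duration from starting to stopping oxygen treatment". Each infant therefore contributes one value in days.

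Statistical analysis fixes the method. The sentence that begins "Comparison of these outcome indicators including duration of oxygen therapy, duration of mechanical ventilation" ends "quantitative scores of chest radiography changes between the intervention and control groups will be conducted using the *t* test". It names no covariate. The repeated measures ANOVA in the same section covers indicators followed over the visits and does not adjust a single duration per infant. On the error rate the section says "Significant differences will be considered at an α level of 0.05"; the number of sides is not stated.

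Table 2 has a row "Ventilator parameters/oxygen therapy" whose first tick is in the Baseline column, and demographic information is taken at screening. Randomization and blinding says "Participants will be randomized into three groups in a 1:1:1 ratio after collection of the baseline data". It mentions no stratification factor.

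Sample size and calculation supplies the planning values: "The cumulative mean duration of severe BPD is reportedly 90 ± 15 days", a fall to 77 days on low dose and to 72 days on high dose, and "the power is set at 0.8". It arrives at 21 per group, raised to 24 for 10% loss.

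**The concern.** The level of support an infant needs at entry, and the infant's age, are natural predictors of how long oxygen will be needed. The article gives reason to expect both to vary. Entrants may be any age from 0 to 1 year. They come from current inpatients, from lists of children discharged within the past year, and from families who respond to notices. Both invasive and noninvasive ventilation durations are secondary outcomes. In addition, if the endpoint's start is the first day of oxygen, some of the duration has already accrued before randomisation for infants on oxygen at entry. Treatment cannot alter that part.

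An unadjusted t test leaves all this variation in the error term. Adjusting for a variable measured before randomisation removes the share of variance it explains and allows for chance differences between arms. The low-dose comparison has the smaller target difference and sets the sample size, so it has the most to gain.

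**Working it through.** **Inputs from Sample size and calculation.** SD 15 days; low-dose difference 90 − 77 = 13 days; high-dose difference 90 − 72 = 18 days; α 0.05; power 0.80; 21 per group before loss and 24 after.

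**Input assumed.** The correlation ρ between the baseline covariate and oxygen duration. The documents give none, so a range of 0.3 to 0.6 is shown.

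**Reproducing the plan's figure.** n per group = 2 × [15 × (1.960 + 0.842) / 13]² = 20.9, rounded up to 21. A one-sided test would give 17, so the plan's figure is two-sided. Allowing for loss, 21 / 0.9 = 23.3, rounded up to 24. For 18 days the same formula gives 10.9, rounded up to 11, so the low dose determines the size. The normal formula gives 80.2% power at 21 per group. The noncentral t, used below because the planned test is a t test, gives 78.2%.

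**Effect of adjustment.** Residual SD = 15 × √(1 − ρ²). The noncentrality is difference / (residual SD × √(2/n)), with 2n − 2 degrees of freedom unadjusted and 2n − 3 with one covariate.

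Example at ρ = 0.5 and n = 21: residual SD = 15 × √0.75 = 12.99. The standard error of the difference falls from 15 × √(2/21) = 4.63 days to 12.99 × √(2/21) = 4.01 days. The noncentrality rises from 13/4.63 = 2.81 to 13/4.01 = 3.24, and power from 78.2% to 88.5%.

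Low dose versus control (13 days):

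| ρ | Residual SD | Power, n = 21 | Gain | Power, n = 24 | Gain |
|---|---|---|---|---|---|
| unadjusted | 15.00 | 78.2% | – | 83.6% | – |
| 0.3 | 14.31 | 81.9% | 3.6 | 86.9% | 3.2 |
| 0.4 | 13.75 | 84.8% | 6.6 | 89.3% | 5.7 |
| 0.5 | 12.99 | 88.5% | 10.3 | 92.4% | 8.8 |
| 0.6 | 12.00 | 92.8% | 14.6 | 95.7% | 12.0 |

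Gains are in percentage points, taken before rounding. A gain of 5 points needs ρ of about 0.36 at n = 21 and 0.38 at n = 24.

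High dose versus control (18 days): at n = 21 power goes from 96.7% to 97.8% (ρ 0.3), 99.2% (ρ 0.5) or 99.7% (ρ 0.6). At n = 24 it goes from 98.2% to 98.9%, 99.7% or 99.9%. The gain is about 1 to 3 points.

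**Cost if the covariates are useless.** With ρ = 0 and three covariate degrees of freedom (for example three support categories plus age), low-dose power goes from 78.24% to 78.08% at n = 21 and from 83.62% to 83.51% at n = 24. The loss is under 0.2 points in both cases.

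**The case against.** The planned test is not an error. It is valid under randomisation and matches the sample size calculation, which reproduces from an unadjusted comparison of two means. Covariate lists are often left to an analysis plan. This stands as far as validity goes. But the article does not leave the method open: it names the t test for this outcome, so a later plan that adopted an adjusted model would depart from it.

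The size of the gain rests on a correlation that no document supplies. Every entrant must have severe BPD and a Silverman-Anderson score above 3, which may narrow the spread at baseline and weaken the correlation. If the population is instead as mixed as the recruitment routes suggest, SD 15 may be too small and the percentages above would shift. Both limits stand, and they are why a range is given.

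Three stronger readings are tempting and are not supported:

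- A reader might infer that randomisation is simple. The article states only the 1:1:1 ratio and that a statistician generates the sequence; blocking or stratification is neither stated nor excluded.
- A reader might infer that the low-dose comparison has no reserve. The plan enrols 24 per arm, and the Withdrawal section replaces participants who leave. With 24 analysed, unadjusted power is 83.6%.
- A reader might infer that chance imbalance biases the t test. Its standard error already allows for such imbalance.

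The covariate cost does not weigh against the change, as the last calculation above shows.

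**Conclusion.** The point holds as one of efficiency, not bias. The protocol fixes an unadjusted test for its primary outcome although a plausible predictor is already collected before randomisation. The gain for the low dose is roughly 3 to 15 points over ρ from 0.3 to 0.6, taking 21 and 24 per arm together. A flat statement that the plan gives up 10 points would go too far: that figure needs both ρ = 0.5, which is assumed, and 21 evaluable per arm rather than the 24 enrolled, where it is about 9. At ρ = 0.3 the gain is under 4 points. For the high dose it is too small to matter.

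These figures also assume SD 15, a two-sided 0.05 test for each pairwise comparison and a linear relation with the covariate. They do not carry over to a time-to-event or ranked form of the endpoint. The change is worth making because it needs no new data and costs almost nothing if the covariates prove weak.

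**What to change.** In Statistical analysis, replace the t test for the primary outcome with a linear model (ANCOVA) of oxygen duration on arm. Name two covariates in advance: level of respiratory support at baseline, from the ventilator and oxygen row of Table 2 with its coding stated, and age at randomisation. State that the values used are those recorded before randomisation, since Table 2 places the Baseline column within the treatment phase. Report each dose-versus-control difference with its confidence interval, and keep the t test as a sensitivity analysis. If the endpoint is later analysed as time to event or by ranks, carry the same covariates into that model.

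The cost is a change of wording and two or three degrees of freedom. No new data are needed. Because the trial is open-label, the covariates and their coding should be fixed before outcome data accumulate, which also rules out choosing them afterwards.

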## Background

Bronchopulmonary dysplasia (BPD) is a common chronic lung disease whose incidence is increasing annually, especially in this time of the two-child policy in China [1, 2]. Patients with BPD usually have ventilator or oxygen dependence during the early stage of the disease [3]. Most patients can gradually withdraw from the ventilator or stop oxygen treatment at different times depending on disease severity, but abnormalities in pulmonary structure and lung function may last until late childhood and even adulthood, especially in those who are diagnosed as severe BPD according to the diagnostic criteria of the National Institute of Child Health and Human Development (NICHD) [4, 5]. The mortality of overall BPD patients is about 15% [6]; nevertheless, the mortality rate of severe BPD reaches 41%, creating an enormous threat to the health of these children [4, 7]. More than 50% of survivors with BPD experience hospital readmission for repeated lower respiratory infections in the first year or two, which causes serious economic and labor burdens on families [4, 8]. Although surfactant treatment [9], prenatal steroid usage [1, 10], ventilator strategies [11], and improved nutrition [12] are used in BPD patients, effective therapies are lacking [13]. Therefore, identifying novel effective therapies for severe BPD in children is urgent and significant.

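### The primary outcome, oxygen duration compared by t test, has no valid value for an infant who dies on oxygen, so it either rewards early death or compares survivors only; the 80% power is conditional on how many die and how they are handled

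*Protocol article*

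**What the plan says.** All places are in the protocol article.

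- **Outcome evaluation:** "The primary endpoint is the cumulative duration of oxygen therapy, i.e., the duration from starting to stopping oxygen treatment". Table 3 gives the time frame as "Until the time of stopping oxygen therapy". Mortality is a separate secondary outcome.
- **Statistical analysis:** the sentence that begins "Comparison of these outcome indicators including duration of oxygen therapy, duration of mechanical ventilation, pulmonary function tests" assigns the t test to intervention against control. Mortality is tested by chi-square, with Kaplan-Meier curves at 24 months. On the level: "Significant differences will be considered at an α level of 0.05".
- **Sample size and calculation:** "The cumulative mean duration of severe BPD is reportedly 90 ± 15 days". The target differences are 90 against 77 days (low dose) and 90 against 72 days (high dose), and "the power is set at 0.8". The result is 21 per group, raised to 24 (72 in total): "To account for the possibility of 10% of patients being lost to follow-up". Nothing is added for death.
- **Background:** "nevertheless, the mortality rate of severe BPD reaches 41" per cent. The figure for BPD overall is about 15%.
- **Withdrawal:** death is among the listed reasons for discontinuation, and a participant who withdraws is replaced by a new one.

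**The concern.** An infant who dies while on oxygen never reaches the event that ends the measured period, yet the t test needs a number for every infant analysed. Two choices fit the text, and neither is sound.

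- **Death counts as the stop.** The infant gets a short duration, which the analysis reads as a good result. A treatment that causes deaths gains; a treatment that prevents them loses.
- **The infant is dropped, or replaced as the Withdrawal section literally reads.** The comparison is then restricted to survivors. If treatment affects survival, the groups compared are no longer those formed by randomisation.

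At stake are the direction of the primary result and the meaning of the stated power.

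**Working it through.** **1. The plan's own figure.** With a two-sided alpha of 0.05, power 0.80 and SD 15, n = 2(1.96 + 0.842)² × 15² / δ².
- δ = 13: 20.9, so 21 per group.
- δ = 18: 10.9, so 11 per group.
- The larger is 21. Then 21 / 0.90 = 23.3, so 24 per group and 72 in total. The stated size reproduces.

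**2. Death counted as the stop.** Assumptions: without death, durations are normal with SD 15 (control mean 90); 24 per arm, because a counted death stays in the analysis; a proportion m die; death is uniform between a fraction a of the infant's own oxygen course and its end. The article gives no timing, so a = 0.5, 0.3 and 0 are shown. The expected mean is 90 × [1 − m(1 − a)/2].

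With no oxygen effect and mortality of 41% against 60%, the spurious advantage of the deadlier arm is 90 × 0.19 × (1 − a)/2:
- a = 0.5: 90 × 0.19 × 0.25 = 4.3 days
- a = 0.3: 90 × 0.19 × 0.35 = 6.0 days
- a = 0: 90 × 0.19 × 0.50 = 8.6 days

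Reversed, a cut in mortality from 41% to 20% with no oxygen effect makes the life-saving arm look worse by 90 × 0.21 × (1 − a)/2 = 4.7, 6.6 or 9.5 days.

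Simulated two-sided t tests (40,000 trials per setting, simulation error below 0.01):

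| Setting | Death in last 50% of course | Last 70% | Any time |
|---|---|---|---|
| 41% v 60% deaths, no oxygen effect: significant in favour of deadlier arm | 11% | 14% | 15% |
| 41% deaths in both arms: power for 13 days | 0.56 | 0.39 | 0.23 |
| 41% deaths in both arms: power for 18 days | 0.84 | 0.66 | 0.41 |
| 15% deaths in both arms: power for 13 days | 0.70 | 0.60 | 0.45 |

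The nominal rate for the first row is 2.5%. Without deaths, the same simulation gives 0.84 for 13 days.

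**3. Deaths dropped and not replaced.** At 41%, 24 × 0.59 = 14.2 infants remain per arm, or 12.7 after a further 10% loss. Power by the noncentral t:
- Low dose (13 days): 0.60, or 0.55 with the 10% loss.
- High dose (18 days): 0.87, or 0.83 with the 10% loss.

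By the normal approximation in step 1, low-dose power passes below 0.80 once fewer than 20.9 infants per arm remain. That is 1 − 20.9/24 = 13% deaths with no other loss, or 1 − 20.9/21.6 = 3% deaths on top of the 10% loss. Keeping 21 evaluable per arm at 41% deaths needs 21 / 0.59 = 35.6, so 36 per arm; with the 10% loss, 21 / (0.59 × 0.90) = 39.5, so 40.

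**4. Deaths replaced.** The number per arm stays at 24. Nominal low-dose power is 0.85 (normal) or 0.84 (t), and after 10% loss 0.81 or 0.79. Power is kept, but for a comparison of survivors.

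**The case against.** **The rate.** The 41% is a literature figure for severe BPD, not a planning rate. What matters is death after randomisation while still on oxygen, which the article does not give. Exclusions such as severe pulmonary hypertension, sepsis and severe intracranial haemorrhage, and recruitment of infants already discharged, could make it lower. This stands, and it is why a range is shown.

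**The timing.** Duration runs from the start of oxygen, but infants are enrolled only after severe BPD is diagnosed, so deaths at the very start of the course cannot enter the data. The right-hand column of the table is therefore near worst case. The direction is the same in every column.

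**The power.** A reader might infer that the trial simply does not deliver 80% power. The document does not support that. The sample size is correct on its own inputs, the high-dose comparison stays above 0.80 when deaths are dropped even at 41%, and replacement restores the number. The shortfall is conditional and mainly in the low-dose comparison, which sets the sample size.

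**Infants still on oxygen at 24 months.** A reader might add them as a second group without a value. Under 90 ± 15 days, about 730 days lies more than 40 SDs above the mean, so this is immaterial.

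**What may sit elsewhere.** Scoring of deaths is commonly left to an analysis plan, which is not shown. Mortality is also reported separately and a monitoring board reviews safety, so an excess of deaths would not be hidden. Both are fair. But the endpoint, the t test and the replacement rule are fixed in this article, and a scoring rule cannot make a start-to-stop mean valid in the presence of deaths without changing one of them. A separate mortality result does not correct the sign of the primary one.

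**Conclusion.** The concern holds for the endpoint and its test, and this needs correction before the analysis. Followed as written, the plan either credits death as a short oxygen course or selects on survival. With death as the stop and mortality of 41% against 60%, a treatment with no effect on oxygen appears 4.3 to 8.6 days better and is significant in its favour in 11% to 15% of trials.

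The power statement needs qualification, not retraction. The 80% holds if few infants die on oxygen, or among survivors only if deaths are replaced. At 41% deaths in both arms, low-dose power is 0.23 to 0.56 with death as the stop and 0.55 to 0.60 with deaths dropped.

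These sizes rest on assumed death times, assumed mortality by arm and the plan's 90 ± 15 days. The direction of the bias does not depend on the particular timing.

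**What to change.** 1. Define the primary outcome as days alive and free of supplemental oxygen from randomisation to one fixed day in all arms (for example the 6-month visit), with death ranked worst.
2. Compare each dose with control by a rank test. Report mortality and oxygen duration in survivors beside it.
3. State in the Withdrawal section that infants who die or withdraw after randomisation stay in the analysis in their assigned arm, and that enrolling a replacement does not remove them.
4. Restate the power for this outcome over a range of mortality, for example 5% to 41%.

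A competing-risk analysis of time to stopping oxygen, with an explicit rule for death, would also answer the main point.

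**Cost.** The endpoint and analysis wording change. Mortality and oxygen therapy are already scheduled at every follow-up visit in Table 2, but dates of oxygen use between visits must also be recorded. The stated power will probably be less favourable, mainly for the low dose. The article reports that recruitment had not begun at submission but gives a start date of July 2019, so the change should be dated relative to the first enrolment.
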